**Figure 2 figure2:**
[figure not shown]
Weekly overview of physical activity performed, as provided to participants in the IT-based intervention group.

Paralleling the 10-week IT-based and print-based interventions, weekly group sessions with up to 25 participants per group were offered separately to both intervention groups. Trained student assistants led these sessions in which participants performed endurance, strength, balance, and flexibility exercises in groups or went for walks in the communities. Each session was 90 minutes long and designed to include 60 minutes of exercise, 10 minutes of answering questions, and 20 minutes of discussion of topics surrounding healthy aging that changed every week (eg, social support, relaxation, pain management). During their first weekly group meeting, participants received the necessary equipment (printed material or information to access the website and/or a Fitbit) and a comprehensive introduction on how to use the equipment and materials. After the first follow-up, interventions continued for another 6 months. After the initial 10 weeks of the interventions, the weekly group meetings were replaced with monthly events held over the course of the following 6 months. During these events, participants of all intervention groups were offered workshops and lectures on lifestyle-related topics, such as healthy nutrition in older age, overcoming loneliness, and strategies for developing healthy habits.

We will develop a toolbox during this project that will include both IT-based and print-based interventions and all related intervention materials that can be used later for long-term implementation and dissemination via different stakeholder groups (for further detail, please see the Discussion).

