### Study Design

After determination of eligibility, study participants were randomized to either an IT-based intervention or a print-based intervention (see Figure 1). In the first group, 30% were randomly selected to receive a PA tracker in addition to access to the website. Weekly time slots were randomly assigned to both intervention groups. Then, we had participants choose appointments according to their personal time constraints without knowing which intervention group they were assigned to. All intervention groups were offered weekly group sessions, and participants were encouraged to attend each of them. Two weeks before the intervention started, participants in all groups attended an introductory event where they were informed about the study background and procedures. On this day, data collection also started, and participants received the activity tracker and questionnaires for the first time (T0). They were also briefed about their randomization to one of the intervention groups and the existence of the other groups. Therefore, they were not blinded. Participants were given the choice to remain in their intervention group or to cross over to the other group after 3 months (and a 10-week intervention period). With that, a crossover design with the following possible combinations was generated: IT-IT, print-print (matched), or IT-print and print-IT. Preferences regarding the intervention material assessed retrospectively at the 9-month follow-up will be taken into account when analyzing intervention effects later in the study. Research staff members conducting the study were not blinded, and the statistician will not be blinded when analyzing the data.

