### Analytic Strategy

Effects of time and group (main outcomes: subjective and objective measures of PA) will be examined in multivariate analyses. In addition, covariates, such as gender, age, and preferences regarding intervention material, and individual contextual factors (eg, living or social environment) will be taken into account. Furthermore, we will analyze how the intervention enables study participants to change their behavior by running mediation analyses. The estimated target sample size of 390 participants for this study is based on the results of 2 recently published studies on PA in adults [27,28] that reported a mean 111 weekly minutes (SD 116.8 weekly minutes) of MVPA and an intervention effect of an increase in MVPA of 77 minutes per week. However, in a conservative (or realistic) approach, we assumed that the mean increase in MVPA in our study will reach only 40 minutes/week. To detect such a difference between the intervention and control groups with a power of 80% at an alpha of .05 (two-sided), a net sample size of 150 subjects for each group is required. Assuming a loss to follow-up from T0 to T1 of 20-25% (ie, ca. 23%), it is necessary to initially recruit 390 study participants (ie, 195 per group at baseline). Assuming another 20% loss to follow-up from T1 to T2, we expect that approximately 240 individuals at T2 will self-select to one of the 4 groups: IT-IT, print-print, IT-print, or print-IT. Should participants self-select equally into each group (n=60), we will still be able to detect the mean difference of 77 minutes/week [28] between each group, by means of an appropriate post hoc test that is adjusted for multiple comparisons.

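### The sample size of 150 per group makes no allowance for session groups nested in arm; the 80% power holds only if the within-group correlation is very small

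*Protocol article*

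**What the plan says.** Three parts of the protocol article bear on this.

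- **Delivery (Methods, Interventions).** During the 10-week programme, "weekly group sessions with up to 25 participants per group were offered separately to both intervention groups". Each session lasted 90 minutes, 60 of them exercise, and was led by trained student assistants.
- **Allocation (Methods, Study Design).** Participants are said to have been randomised to IT or print. The same paragraph adds: "Weekly time slots were randomly assigned to both intervention groups". Participants then picked appointments that suited them, unaware of the arm.
- **Sample size (Methods, Analytic Strategy).** The cited studies "reported a mean 111 weekly minutes (SD 116.8 weekly minutes) of MVPA", and for the effect "we assumed that the mean increase in MVPA in our study will reach only 40 minutes/week". To detect this difference between groups "with a power of 80% at an alpha of .05 (two-sided), a net sample size of 150 subjects for each group is required". The only inflation is for dropout: "Assuming a loss to follow-up from T0 to T1 of 20-25% (ie, ca. 23"%), so that "it is necessary to initially recruit 390 study participants (ie, 195 per group at baseline").

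The sample size paragraph names no ICC, design effect, group size or number of groups.

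**The concern.** People who exercise together weekly for 10 weeks share peers, sessions and discussion. The primary outcome is physical activity itself, so outcomes within a session group may be correlated. Because each group belongs to one arm only, variation between groups adds directly to the variance of the IT versus print difference. A calculation that treats 150 people per arm as 150 independent observations leaves this out.

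At stake is the main comparison of the trial. If the correlation is not negligible, the power for 40 min/week is below the stated 80%, and an analysis that ignored the groups would give standard errors that are too small.

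The allocation text adds a second question. Slots were assigned to arms and participants chose slots, so the article does not show whether arm was already fixed when the slot was chosen or was settled by that choice. In the second case the slot is the unit of randomisation.

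**Working it through.** **Inputs from the article:** difference 40 min/week, SD 116.8, two-sided alpha 0.05, power 80%, 150 analysed and 195 recruited per group, loss about 23%, groups of up to 25.

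**Assumed, because the article does not give them:** ICC 0.01, 0.02 and 0.05; groups full at baseline; for one line below, a correlation of 0.5 between T0 and follow-up MVPA.

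**1. The plan's own figure.** n per group = 2 × (116.8 × (1.960 + 0.842) / 40)² = 133.8, so 134; the t-test version gives 134.8, so 135. The stated 150 is not reproduced. Under independence, 150 per group has about 84% power. The dropout step does reproduce: 150 / 0.77 = 194.8, so 195 per group and 390 in all.

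**2. What the surplus covers.** 150 / 133.8 = 1.12. With design effect DE = 1 + (m − 1) × ICC, the break-even ICC is 0.12 / (m − 1):

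- m = 25: about 0.005
- m = 19: about 0.007 (about 0.006 from the t-test base of 134.8)
- m = 10: about 0.013

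**3. Group size.** 195 / 25 = 7.8, so at least 8 groups per arm. At T1, 150 / 8 = 18.75 analysed per group.

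**4. Power at 150 per group, m = 18.75.** The standard error of the difference is 116.8 × √(2 × DE / 150). "Design effect alone" uses the normal approximation with n = 150 / DE. "Group-level df" uses the noncentral t with 2 × 8 − 2 = 14 degrees of freedom. The adjusted column multiplies the variance by 1 − 0.5² = 0.75 and keeps 14 df.

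| ICC | DE | Design effect alone | Group-level df | Group-level df, T0-adjusted (r = 0.5) |
|---|---|---|---|---|
| 0.01 | 1.18 | 78% | 72% | 84% |
| 0.02 | 1.35 | 72% | 66% | 78% |
| 0.05 | 1.89 | 58% | 52% | 64% |

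The break-even values in step 2 belong to the design-effect method. With 14 df and no adjustment, power is already about 79% at ICC 0.

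**5. Sensitivity to group size, design effect alone.** With m = 25, power at the three ICCs is 76%, 68% and 52%. With m = 10 it is 81%, 78% and 69%.

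**6. Size of the test if groups were ignored.** True size = 2 × (1 − Φ(1.96 / √DE)). With m = 18.75 this is about 7%, 9% and 15% for a nominal 5% test.

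**The case against.** The strongest reply is that the shortfall is conditional. The article gives neither an ICC nor a mean group size, and 25 is a ceiling, so 8 full groups per arm is the fewest and largest the text allows. With 10 analysed per group and ICC 0.01, power by design effect alone is still 81%. Baseline data are collected and change in activity is the primary outcome; at an assumed r of 0.5, adjustment restores 84% at ICC 0.01. All of this stands, and it rules out saying flatly that the stated power is not delivered.

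A session-group term may also sit in a statistical analysis plan that is not shown. The article speaks only of multivariate analyses of time and group. Its silence on the term is therefore not counted as an error, and the inflated test size holds only if the final analysis ignores groups.

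A reader might infer more than the text supports on three further points:

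- **Each group had its own leader and place.** The article says only that trained student assistants led sessions; leaders could have served several groups or both arms.
- **Time of day is confounded with arm.** Slots were assigned at random and chosen without knowledge of the arm, so only chance imbalance between slots can be claimed.
- **The trial was cluster-randomised.** The article says participants were randomised, and its wording is compatible with arm being set before the slot was chosen. The order is unclear, but allocation by slot is not established.

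What the reply does not remove is that a completed sample size calculation stands in the article and allows only for dropout, beside a design with session groups nested in arm.

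**Conclusion.** The point holds in conditional form. The sample size treats participants as independent although each arm is delivered in its own session groups. The surplus of 150 over about 135 is unexplained and is not attributed to clustering. By the design-effect formula it would cover an ICC of only about 0.005 to 0.007 for groups of 19 to 25. Above that, unadjusted power is below 80% at those group sizes. How far below depends on the ICC, the number and size of groups, the degrees of freedom and any baseline adjustment, none of which the article fixes. Separately, the order of slot choice and arm assignment needs clarifying. Data collection ended in January 2020, so recruitment cannot change; what can change is the analysis and how the power is reported.

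**What to change.** 1. Analyse IT versus print with a random intercept for session group (time slot), small-sample degrees of freedom and adjustment for T0 MVPA. If the analysis plan already does this, say so in Analytic Strategy.
2. Restate the power there for ICC 0.01 to 0.05, using the actual number and size of groups, and explain why 150 is stated where the inputs give about 135.
3. State in Study Design whether a participant's arm was fixed before the slot was chosen or by that choice. If by the choice, describe the trial as randomised by time slot.

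The cost is one random effect, for which slot membership should be on record, slightly wider confidence intervals and a less favourable stated power.

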### Ethics Statement and Consent

Ethical approval was obtained from the Medical Association in Bremen (RA/RE-635, on July 3, 2018). The study was registered with the German Clinical Trials Register on January 10, 2019 – number DRKS00016073. All study participants were fully informed about the study and were requested to give informed consent.

## Results

In this study, we refined the previously developed IT-based intervention and translated it into a simple print-based intervention during the development phase from February 2018 to December 2018. The results of the qualitative focus groups held in May and June 2018 were analyzed and used to refine the existing intervention and to develop the print-based intervention. During the implementation phase of the study (baseline: January to April 2019; 3-month follow-up: April to July 2019; 9-month follow-up: September 2019 to January 2020), we expect to observe significant increases in PA at the 3-month follow-up after participation in both the print-based and IT-based interventions, in comparison with baseline, and a larger increase in PA in the 2 intervention groups than in the delayed-intervention control group of the preceding study (PROMOTE I).

We further expect that by providing some degree of choice to study participants 3 months into this study, we will be able to reduce loss to follow-up and improve long-term program adherence, when compared with the previous study. Further, we assume that participants with a ≥25% increase in PA level from baseline to the end of the follow-up period in the pooled sample across the 2 funding phases (ie, PROMOTE I sample and the subsample in PROMOTE II) will display significant improvements in indicators for healthy aging, such as cognitive function. Data collection was completed on January 31, 2020. Data cleaning and analysis started in February 2020. We expect to publish the first results of the study by the end of the funding period (January 2021).

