**Methods:**

Our target sample size was 390 initially inactive community-dwelling older adults aged ≥60 years at baseline (3-month follow-up [T1]: expected n=300; 9-month follow-up [T2]: expected n=240) who were randomized to one of two interventions for self-monitoring PA: IT-based (50%) or print-based (50%) intervention. In addition, 30% of the IT-based intervention group received a PA tracker. At T1, participants in both groups could choose whether they prefered to keep their assigned intervention or cross over to the other group for the following 6 months (T2). Participants’ intervention preferences at baseline were collected retrospectively to run a post hoc matched-mismatched analysis. During the initial 3-month intervention period, both intervention groups were offered weekly group sessions that were continued monthly between T1 and T2. A self-administered questionnaire and 3D accelerometers were employed to assess changes in PA between baseline, T1, and T2. Adherence to PA recommendations, attendance at group sessions, and acceptance of the interventions were also tracked.

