Two studies investigated the added benefit of using Fitbit activity trackers in addition to a website to monitor PA on total weekly PA levels and moderate-to-vigorous PA (MVPA) [18,19]. In a sample of overweight adults, Vandelanotte et al [18] demonstrated a significant increase in total weekly PA and MVPA after 3 months for a group of participants using a Fitbit compared with a group of participants not using a Fitbit. Although sitting time decreased over time, this effect was not significant [18]. With a sample of older adults, Muellmann et al [19] found no significant differences in PA levels between a group using a Fitbit compared with a group not using a Fitbit. However, participants in the Fitbit group had slightly greater increases in MVPA and decreases in sedentary time than participants in the non-Fitbit group after 3 months [19]. While more participants in the non-Fitbit group did not complete the follow-up after 3 months than in the Fitbit group (63% vs 36%) in the first study [18], the reverse was true in the second study [19]. More participants in the Fitbit group did not complete the 3-month follow-up than in the non-Fitbit group (40% vs 31%) [19]. It is conceivable that individual preferences for interventions may have influenced dropout and possibly adherence to the interventions [10,11,13]. Participants may have been randomized to an intervention that they would not have picked had they been given a choice and that they may have found difficult to interact with.

The effects of study participants’ preferences on treatment or intervention outcomes in randomized controlled trials are still not well understood [20,21]. There is some indication that the preferences for delivery mode vary by the sociodemographic characteristics of participants, such as age, gender, and living environment, or by weight status [13,22]. For example, preference for an IT-based intervention was positively related with being 35 years or older (compared to younger ages) and high levels of internet use and was negatively associated with female gender. Preference for a print-based intervention was associated with older age and negatively associated with female gender and obesity [22]. Further, evidence suggests that sociodemographic variables may explain variations in the use of PA trackers [23] and that use of trackers in PA interventions should be aligned with preferences of different target groups [13].

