## Methods

The study is embedded in the larger Physical Activity and Health Equity: Primary Prevention for Healthy Ageing (AEQUIPA) research network that is funded by the Federal Ministry of Education and Research (BMBF) [24]. The AEQUIPA research network is comprised of six subprojects and conducts theory-based and participatory empirical research on different aspects of PA and healthy aging in the northwestern part of Germany [24]. One of the aims of the network is to develop, implement, and evaluate PA interventions for the primary prevention of chronic diseases in adults aged at least 65 years. The first 3-year funding phase was completed in January 2018 [25]. The topic of the research remains the same in the second funding phase (2018-2021); however, in this phase, additional aims are to intensify community participation to reach physically inactive adults, use appropriate technology for PA promotion in the population of older adults, and disseminate and transfer PA interventions as well as results of both funding phases. This study (PROMOTE II) is one of the 6 subprojects of the entire network and builds on knowledge gained during the preceding study (PROMOTE I) [19,25,26].

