In the previous study, the research aims were to develop and test 2 individually tailored IT-based interventions for the promotion of a physically active lifestyle in adults aged 65-75 years in a community-based intervention trial [25]. Intervention effects on physical, psychological, and cognitive indicators for healthy aging were examined by comparing 2 intervention groups to a delayed-intervention control group [26]. Results of this trial are reported elsewhere [19,26]. Briefly, the proportion of already active intervention participants at baseline was relatively high. At follow-up, they reported increased social-cognitive predictors for behavior change, but no significant increases in the primary outcome of MVPA when compared with the control group. Also, the dropout rate was higher in the group invited to use PA trackers in addition to the IT-based intervention compared with the IT-only intervention suggesting that individuals with little technological experience might have been randomized to an intervention that they found too difficult to use. In addition, participants in both intervention groups requested printed diaries to track their PA during times that they had limited access to computers. Thus, reactions of the target population during the first funding phase suggested that a proportion of participants prefers a print-based intervention or would appreciate an app for accessing a PA diary on their smartphone or tablet.

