### Measures

The primary outcome is change in PA, which is assessed at baseline, 3 months, and 9 months using triaxial accelerometers worn at the right hip during the day over the course of 7 days and a self-administered questionnaire. Participants received the self-administered questionnaire and accelerometer at their introductory event at baseline (T0), after 3 months (T1) at their tenth group meeting, and after 9 months (T2) at their last monthly meeting. Further, due to cost issues, a random subsample of 114 participants (equally distributed across the intervention groups) underwent additional anthropometric, physical fitness, and cognitive tests to assess secondary outcomes at all 3 time points. Physical fitness was assessed using gait speed via a 4-meter walk test [29], handgrip strength using a dynamometer [30], and cardiovascular fitness using the 2-minute step test [31]. Additionally, participants’ weight was assessed using a scale. Attention and inhibition were assessed using a cognitive test (Simon task) [32].

Data from the objective measures of physical fitness and cognitive performance (Mini Mental State Examination and executive function test) will be preprocessed using customized MATLAB routines and analyzed using multivariate generalized linear models. Data for physical fitness and cognitive performance assessed at baseline and after the 10-week intervention during the first funding phase and in the subsample of participants during the second funding phase will be pooled to increase power for data analysis and to meet sample heterogeneity. Further, the larger sample size will enable us to conduct subgroup analyses with respect to motivational stage, activity behavior, and social engagement.

All participants underwent a short version of the Mini Mental State Examination during their first weekly group meeting [33]. Motivational stages to engage in recommended PA (endurance, strength, flexibility, and balance training), social-cognitive predictors for behavior change, and psychosocial factors (eg, quality of life, depression) were assessed in the self-administered questionnaire (for further detail on the instruments included in the questionnaire, see Table 1).

**Table 1 table1:** Measures assessed in the self-administered study questionnaire.

Outcome measure		Instrument/scale	Time of assessment

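### The expected gain in retention over PROMOTE I cannot be credited to choice at month 3, because neither follow-up interval offers a contrast that isolates choice

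*Protocol article*

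**What the plan says.** All references are to the protocol article.

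- **Retention claim (Results).** The trial team expects that "by providing some degree of choice to study participants 3 months into this study, we will be able to reduce loss to follow-up" and also improve long-term adherence. The stated comparator is the previous study.
- **Which study that is (Methods, opening paragraph).** The present trial "builds on knowledge gained during the preceding study (PROMOTE I) [19,25,26". Reference 19 is also the second of the two tracker studies described in the Introduction.
- **Its reported losses (Introduction).** For that study: "More participants in the Fitbit group did not complete the 3-month follow-up than in the non-Fitbit group (40% vs 31" percent). PROMOTE I was evaluated by "comparing 2 intervention groups to a delayed-intervention control group" (Methods). No loss is given for the control group.
- **Its follow-up, as far as shown (Measures).** The fitness and cognition data to be pooled were "assessed at baseline and after the 10-week intervention during the first funding phase".
- **When choice begins here (Study Design).** "Participants were given the choice to remain in their intervention group or to cross over to the other group after 3 months". The option was open to both arms.
- **Attrition assumptions (Analytic Strategy; Abstract, Methods).** "Assuming a loss to follow-up from T0 to T1 of 20-25% (ie, ca. 23" percent), then a further 20% to T2, which gives "3-month follow-up [T1]: expected n=300; 9-month follow-up [T2]: expected n=240". No source is given for either rate, and neither is tied to choice.

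**The concern.** To credit choice with better retention, one needs an interval in which choice could act and a comparator without choice over that same interval. The article provides the two only separately. Before month 3 there is a predecessor figure but no choice yet. After month 3 there is choice but no predecessor figure, and no arm here without the option.

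The article's own account of the earlier dropout sharpens this. The Introduction and Methods suggest that people left because they had been randomised to something they would not have picked or found too hard to use. That is early loss, and this design again randomises everyone for the first three months.

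At stake is a conclusion about the value of a preference-based design, which the Discussion presents as one of the things the study hopes to inform. If the Results sentence is carried into the report, any lower loss than in PROMOTE I could be read as an effect of choice when other differences explain it equally well. Separately, the 23% planning figure lies below both early losses the article reports for the predecessor's IT arms, and the article does not explain why.

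**Working it through.** **1. The two intervals side by side**

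| Interval | Could choice act here? | PROMOTE I loss shown | Concurrent arm without choice |
|---|---|---|---|
| T0 to T1 (months 0-3) | Not yet offered | 40% tracker, 31% no tracker (IT arms only) | Choice does not yet apply to anyone |
| T1 to T2 (months 3-9) | Yes | None | None; all are offered it |

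Neither row contains both an exposure to choice and a comparator without it. A crude T0-T1 comparison with PROMOTE I is possible, but it also differs in the new print arm, the simplified IT intervention (Study Aims), age (60 and over here, 65-75 there) and the exclusion of people already active.

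**2. Reproducing the plan's attrition chain**

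- 300 / (1 − 0.23) = 390 recruited.
- 390 × (1 − 0.23) = 300 at T1.
- 300 × (1 − 0.20) = 240 at T2.

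The chain is internally consistent and makes no use of the choice argument.

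**3. Sensitivity to the predecessor's IT-arm rates**

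Inputs: 195 per arm; 30% of the IT arm with a tracker; losses of 40% and 31% (Introduction); the plan's 20% second-stage loss; difference 40 min/week; SD 116.8; two-sided alpha 0.05 (Analytic Strategy).

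- IT-arm loss = 0.30 × 40% + 0.70 × 31% = 33.7%.
- IT arm at T1 = 195 × 0.663 = 129.3.
- Print arm at the planned 23% = 195 × 0.77 = 150.2.
- T1 total = 279.4; T2 total = 279.4 × 0.80 = 223.5.
- Print loss needed for 300 still to remain at T1: 2 × 23.1% − 33.7% = 12.5%.

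Power by the normal approximation = Φ(40 / [116.8 × √(1/n₁ + 1/n₂)] − 1.96):

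| Scenario | n at T1 (IT / print) | T1 total | T2 total | Power |
|---|---|---|---|---|
| As planned | 150 / 150 | 300 | 240 | 84.3% |
| IT 33.7%, print 23% | 129 / 150 | 279 | 224 | 81.4% |
| Both 31% | 135 / 135 | 269 | 215 | 80.2% |
| IT 33.7%, print 31% | 129 / 135 | 264 | 211 | 79.4% |
| Both 33.7% | 129 / 129 | 259 | 207 | 78.6% |
| Both 40% | 117 / 117 | 234 | 187 | 74.5% |

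A t-test gives slightly lower values where it was run: 84.0%, 81.1%, 78.2% and 74.2% for rows 1, 2, 5 and 6. At 31% in both arms power is therefore at the 80% line rather than clearly above it.

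The effect is modest because the stated inputs require only 2 × (1.96 + 0.84)² × 116.8² / 40² ≈ 134 per group, not the stated 150, and the surplus absorbs part of the loss. With the IT arm at 129.3, power reaches 80% when 1/129.3 + 1/n = 2/134, so n ≈ 139. That corresponds to a print loss of 1 − 139/195 ≈ 29%.

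**The case against.** The strongest reply is that the Results sentence is only an expectation. Retention is not among the study aims, has no planned test in Analytic Strategy and is not listed as an outcome under Measures. Because the sentence also mentions long-term adherence, it can be read as covering all nine months. This is fair: a reader might infer that the plan will test choice on T0-T1 loss, and no passage says so. It does not rescue the attribution, since the sentence names choice as the cause and PROMOTE I as the comparator, and no interval supports that link.

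Second, participants were briefed at an introductory event before the intervention began. If the later option to switch was mentioned, anticipation could have affected early retention. The article does not say either way, so it is too strong to hold that choice cannot have influenced T0-T1 loss. Anticipation would still leave no comparator that separates it from the other differences.

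Third, PROMOTE I is reported elsewhere, and a later loss figure may exist there. That stands. The point is limited to what the article shows, and such a figure would still be historical.

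Fourth, a reader might infer that the expected 300 and 240 contradict the article's own evidence. They do not:

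- The 31-40% covers only PROMOTE I's two IT arms.
- Half of this sample is print, for which no loss rate in this population is given.
- Trackers go to 30% of the IT arm, about 15% of the whole sample.
- The IT intervention was simplified in response to earlier experience.
- Nothing in the article contradicts the 20% loss from T1 to T2; 240 is open to question only because it starts from 300.

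Finally, the Discussion already concedes that lacking a control group limits interpretation of positive effects. It does not extend this to retention.

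**Conclusion.** The attribution of better retention and adherence to choice at month 3, relative to PROMOTE I, is unsupported by the design and by the figures shown. This rests on the timing of choice, on the absence of any months 3-9 loss for PROMOTE I in the article, and on choice being offered to every participant. It requires no assumption about actual dropout.

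The loss assumption is a secondary and minor matter. The 23% is unsourced and lies 8 to 17 percentage points below the predecessor's IT-arm rates. It is in tension with them but not refuted by them. If PROMOTE I's rates recur in the IT arm only, and print loses the planned 23%, power is about 81%, so the stated 80% is not shown to fail. It falls below 80% only if the print arm also loses at close to the IT-arm rate (above roughly 29% on the plan's inputs), for example about 78-79% when both arms lose 33.7%. The 74-75% case applies the tracker users' rate to everyone, which no passage supports.

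**What to change.** 1. **Results section.** Withdraw the attribution of lower loss and better adherence to choice.
2. **Reporting.** Give T0-T1 loss by randomised arm, as a randomised comparison of IT with print. Give T1-T2 loss descriptively, without crediting choice. Label any comparison with PROMOTE I as historical and confounded by age range, activity at entry and intervention content.
3. **Analytic Strategy (minor).** State the rationale for the 23% loss to T1, or show the sensitivity: IT 33.7% with print 23% gives about 279 at T1, 224 at T2 and power of about 81%; 33.7% in both arms gives about 259, 207 and 78-79%.

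The cost is wording and a few recalculated figures. No participants or procedures are added. Data collection ended on January 31, 2020 and results were still to be published, so items 1 and 2 can still shape the report. Item 3 now bears only on how the planning is described.
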